## 1. SUMMARY

**Background:** Adjusting to MS can be highly demanding, and the disease can be a consistent source of stress. Resilience is an internal resource for alleviating the adverse effects of stress and sustaining good mental health through adversity.

In recent years, an Australian team developed and tested an Acceptance and Commitment Therapy (ACT)-based group resilience-training program: the REsilience and Activities for every DaY (READY). In view of the promising preliminary data on the READY for MS resilience training intervention, we decided to apply the READY for MS in Italy and to evaluate the efficacy of the program by following the Medical Research Council (MRC) framework for developing and evaluating complex interventions.

The project is composed of two phases: 1) a pilot randomized controlled trial (RCT) with a nested qualitative study; 2) a multicenter phase III RCT, with an ancillary study on the impact of the training on the psychologists who will learn and deliver the READY for MS program.

Results from phase 1 showed that Italian READY for MS was well accepted by MS patients. Qualitative (but not quantitative) data provided evidence in favour of READY. Our findings informed methodological and intervention refinements for the multi-centre RCT (phase 2).

**Aim:** This study aims to evaluate the efficacy of the Italian READY for MS program in a multi-center RCT. Our primary end-point is the between-arm difference in T0 - T2 changes in CD-RISC 25 score.

**Methods:** This is a multi-centre RCT assessing the superiority of Italian READY for MS over relaxation in a sample of 240 people with MS. Groups will be allocated to Italian READY for MS or control intervention in a 1:1 ratio.

*Study Intervention.* READY for MS is an adult ACT informed group resilience training program which consists of seven weekly 2.5 hour sessions plus a 2.5 hour 'booster' session approximately five weeks after the seventh session. Content of the seven weekly sessions is as follows: an introductory module (Introduction to the READY Resilience Model), five modules focusing on each of the six ACT processes (Mindfulness, Acceptance, Cognitive Defusion, Self-as-Context, Values and Meaningful Action), and a review module (Review and Future Planning).

*Control Intervention.* The control condition consisted of a group relaxation program based on autogenic training. The intervention consisted of seven, 1-hour weekly group sessions, followed by a 'booster' session approximately after five weeks (S3 Appendix - Relaxation sessions). This control program matched the study intervention in number of sessions and schedule (but not in session content and length).

*Trial outcomes.* Patient reported outcome measures (PROMs) will be assessed immediately before, after the booster session, at three and six month follow-up. Additional process data will capture participants' attendance, homework completion, and facilitator perspectives on a weekly basis. Each session will be audio recorded and self-rated by the facilitators. Two sessions for each Italian READY for MS group will be randomly selected and independently rated by two ACT experts to assess intervention fidelity. The control group session fidelity will be assessed following the same procedures except for the use of ACT-FM and audio recording assessment that will be done by one rater.

*Data analysis.* Longitudinal changes will be analyzed using repeated measures hierarchical (patients nested in clusters) generalized linear mixed models, accounting for the cluster effect (using a random intercepts for clusters). All group comparisons will be carried out according to the intention-to-treat principle.

**Discussion:** This study will produce evidence on the efficacy of a brief, structured group intervention to promote resilience in people with MS by comparing it with an active group intervention. It is expected that, by empowering participant inner resources, Italian READY for MS can promote a personal growth that may help participants to prevent or overcome difficulties in adjustment to MS, and to live a full and rich life. The Italian READY for MS program is brief and highly structured, which ease its affordability.

**Trial registration:** (ISRCTN registry) TBD

**Keywords:** Multiple sclerosis, Resilience, Randomized controlled trial, Acceptance and Commitment Therapy, Complex intervention.

## 2. INTRODUCTION

Multiple sclerosis (MS) is an inflammatory, progressive demyelinating disease of the central nervous system. With a lifetime risk of 1 in 400, it is the most common cause of progressive neurological disability in young adults [1]. The most recent study on the global prevalence of MS estimated that approximately 2.3 million people worldwide have MS, with Canada, USA and some European countries, including Italy, having the highest prevalence rates [2]. The Italian MS Foundation estimated that there are more than 122,000 persons with MS (PwMS) in Italy [3]. Given that MS typically manifests in young adulthood [4], the impact of diagnosis is particularly distressing as it has the potential to significantly interfere with life goals [5], and negatively impact on work-related activities [6]. Patients' experience of MS is characterized by remissions, relapses, possible persistent disability and continuous progression. As a result, PwMS often have to deal with uncertainty about disease progression, loss of function, changes in life roles and a variety of symptoms [7]. For these reasons, adjusting to MS can be highly demanding [8], and the disease can be a consistent source of stress. In fact, PwMS have poorer quality of life (QoL) than healthy controls and people with other chronic diseases; lifetime prevalence is approximately 50% for depressive symptoms and 35% for anxiety disorders [9, 10]. In addition, evidence suggests an association between psychological stress and subsequent relapses in MS, with the occurrence of stressful life events purported to lead to a greater risk for relapses [11].

Resilience is an internal resource for alleviating the adverse effects of stress and sustaining good mental health through adversity [12]. It entails the process of negotiating, managing and adapting to significant stressors or trauma through drawing on internal (i.e. mindfulness, acceptance, cognitive flexibility and active coping), and external (i.e. social support, financial capital and community services) resources [13]. In times of adversity, people with low resilience have a higher risk of experiencing poor QoL, emotional burden and interpersonal difficulties [14]. Moreover, they can adopt health compromising behaviors and experience somatic complaints and poor physical health [15]. Prolonged stress together with poor psychosocial functioning may negatively affect physical health through different mechanisms, such as hypertension and blood pressure reactivity to stress, pro-inflammatory cytokines and the development of metabolic syndrome [16]. Given that PwMS have lower resilience than community samples and people with other chronic illnesses [17], they are particularly vulnerable to low QoL and well-being. Therefore, targeted interventions aimed at fostering resilience are crucial in helping PwMS deal with their illness-related stressors and improve their QoL.

Leppin et al's [12] meta-analysis of resilience training programs in adults showed modest but consistent benefits in improving a number of mental health outcomes. A more recent review demonstrated that resilience training promotes a range of positive psychosocial outcomes in people with chronic illnesses [18]. Resilience training programs have been shown to improve QoL, anxiety, depression, perceived stress and well-being in adults with cancer [19, 20, 21], congenital heart disease [22], diabetes [23], and neurofibromatosis [24]. Despite these promising findings, a recent narrative review of resilience training identified numerous methodological limitations. First, evidence of the benefits of resilience training remains limited; second, resilience training interventions are often not well differentiated from other forms of training; third, the effects of the training on psychological functioning are strongly influenced by the outcome measures selected and the setting of the training [25].

In recent years, an Australian team developed and tested an Acceptance and Commitment Therapy (ACT)-based group resilience-training program: the REsilience and Activities for every DaY (READY). The READY program was initially trialed in a workplace setting [26, 27] and then adapted and successfully applied to different health conditions: cancer [28] diabetes [29] and MS [30]. Findings showed READY for MS had beneficial impacts on resilience, QoL, depression, stress and protective factors (managing difficult thoughts, values and acceptance) in PwMS [30]. READY for MS is based on ACT which is a recent variant of cognitive behavior therapy. ACT is informed by the psychological flexibility framework. Psychological flexibility is defined as “the ability to contact the present moment more fully as a conscious human being, and to change or persist in behavior when doing so serves valued ends” [31]. It is fostered by six ACT processes: (1) acceptance – openness to experience, (2) cognitive defusion – observing thoughts rather than taking them literally, (3) present moment awareness – mindfulness, (4) self as context – contact with a sense of self that is continuous and provides flexible perspective taking, (5) values – freely chosen personally meaningful life directions, (6) committed action – values-guided effective action [31]. Each process has been shown to be related to better mental health, lower risk of disease, better health outcomes for those already diagnosed with illness [29, 31-34]. Psychological flexibility plays a key role in promoting resilience [35]. Furthermore, psychological flexibility processes have been shown to mediate the beneficial effects of resilience training in PwMS [30].

In view of the promising preliminary data on the READY for MS resilience training intervention and taking into consideration the limitations highlighted by Forbes and Fikretoglu [25], we decided to apply the READY for MS in Italy and to evaluate the efficacy of the program by following the Medical Research Council (MRC) framework for developing and evaluating complex interventions, which has a phased approach, from a pre-clinical research phase to a final phase in which the intervention is introduced into the health service, leading to a theory-driven intervention: a "bottom up" development which guarantee to enter a phase III trial with an appropriate theory and pilot work [36]. Further, both quantitative and qualitative methods are used and integrated within the framework, in order to better appraise the effects of the (complex) intervention as a whole and its components. For this reason, the project evaluating the Italian version of the READY for MS program is composed of two phases: 1) a pilot randomized controlled trial (RCT) with a nested qualitative study; 2) a multicenter phase III RCT, with an ancillary study on the impact of the training on the psychologists who will learn and deliver the READY for MS program.

The pilot, single blind RCT with a nested qualitative study comparing Italian READY for MS with relaxation (phase 1) was run between April 2017 and January 2018 at the Fondazione IRCCS Istituto Neurologico Carlo Besta. Four intervention groups were conducted with 39 participants (20 Italian READY for MS, 19 relaxation). Two patients assigned to Italian READY for MS withdrew before beginning the intervention due to unexpected work commitments. The Italian READY for MS program was well accepted by MS patients with varied socio-demographic and clinical characteristics, suggesting it has high utility and acceptability in an Italian clinical setting. There was an improvement of the primary and in most of the secondary outcome measures over time, which did not differ statistically between the Italian READY for MS and group relaxation. Qualitative data indicated that Italian READY for MS was viewed as superior to relaxation by participants assigned to relaxation who, at the end of the trial, received Italian READY for MS. This finding converges with four non-significant statistical trends supporting the efficacy of Italian

READY for MS. Consistent with the ACT psychological flexibility framework, the qualitative data indicated that participants' perceived improvements in resilience and QoL were due to the acquisition of skills related to the six core ACT processes. Findings informed methodological and intervention refinements for the multi-centre RCT evaluation of the Italian READY for MS program (phase 2).

## **2.1 From a pilot to a multi-center RCT**

Data from the Pilot RCT were discussed in a dedicated meeting with an International Panel. The meeting focused on the design of the next multi-centre READY for MS RCT. It was a structured discussion, using a "PICO" (Population, Intervention, Comparator, Outcomes) format [37]. The panel reached the following conclusions:

**Population.** The eligibility criteria of the pilot RCT were deemed adequate by the panel.

**Intervention.** The panel agreed on confirming the program in its current format.

**Comparator.** Participants will be allocated to Italian READY for MS or control group (relaxation) in a 1:1 ratio. Control intervention facilitators should not have training in mindfulness or ACT, in order to prevent contamination. The experimental and comparator interventions will be delivered by different people.

**Outcome measures.** Following Chmitorz et al. suggestion [38] and based on the trend differences observed in the pilot RCT, the Connor-Davidson Resilience Scale 25 (CD-RISC 25) [39] was chosen as primary outcome.

The sample size presented in this study protocol was calculated on pilot RCT data in terms of change in CD-RISC 25 at 3-month follow-up, and using a conservative approach (assuming an Intraclass Correlation (ICC) equal to 0.10, instead of .07; power higher than .91, instead of .80; assuming a drop-out rate of 25%).

## **3. AIM**

This study aims to evaluate the efficacy of the Italian READY for MS program in a multi-center RCT. We hypothesize that participants in the Italian READY for MS would show higher improvements on the primary outcome of resilience (CD-RISC 25 [39]) and on the secondary outcomes of mood (The Hospital Anxiety and Depression Scale, HADS [40]; The Positive and Negative Affect Schedule, PANAS [41]), health related quality of life (54-items MS Quality of Life inventory, MSQOL-54 [42]; the European Quality of life Five Dimensions, EQ-5D-3L [43]), well-being (The short form of the Mental Health Continuum, MHC-SF [44]), and psychological flexibility (The Comprehensive assessment Acceptance and Commitment Therapy processes, CompACT [45]), compared to the control group (relaxation).

## **4. ENDPOINTS**

### **4.1 Primary Endpoint**

Our primary end-point is the between-arm difference in T0 - T2 changes in CD-RISC 25 score.

### **4.2 Secondary Endpoints**

- Differences between changes in CD-RISC 25 scores at post intervention (T1) and 6-month follow-up (T3) between Italian READY for MS and relaxation groups.

- Differences between changes in HADS, PANAS, MSQOL-54 (mental health component, MHC; physical health component, PHC), EQ-5D-3L, MHC-SF, CompACT scores at different time-points between Italian READY for MS and relaxation groups.

## 5. MEASURES TAKEN TO MINIMIZE BIAS

The study follows the CONSORT guidance for RCTs on social and psychological interventions (CONSORT-SPI 2018) [46]. This includes the devise of the study protocol following the SPIRIT guidance [47], protocol's publication, and the trial public registration (ISRCTN registry).

Blinding of patients is not possible due to the type of the study intervention. The statistical analyses will be performed by study personnel blind to the participants' randomization to either the intervention group or the control group and who are not involved in providing treatment. All study personnel will be trained to conform to Good Clinical Practice (GCP) regulation. Electronic version of the study PROMs will be used to ensure the high quality of the entered data. The Coordinating Unit will monitor adherence to the study protocol and overall study quality. Finally, an Independent Data and Safety Monitoring Committee (IDSMC) will oversee the study procedures, recruitment, and data flow. The Clinical Psychology Expert Panel will monitor the intervention fidelity audio recording and rating Italian READY for MS and Relaxation sessions.

The following meetings are scheduled:

1. *Investigators meeting.* It will be run via teleconference. All the centres PIs, facilitators (both Italian READY for MS and control group) and Trial Steering Committee (TSC) members will be invited. The aim of this meeting is to provide clear information on the study procedures.
2. *Facilitators meetings.* Facilitators will receive detailed information only on the group intervention (Italian READY for MS or relaxation) they will run. For this reason, facilitator meetings will be run separately for Italian READY for MS and relaxation facilitators.
  - a. *Relaxation facilitator meetings.*
    - i. A teleconference dedicated to the presentation of the relaxation program will be organized before the beginning of the intervention.
    - ii. A second meeting will be run after the 3rd session in order to monitor possible difficulties, top up facilitators motivation and provide a safe place for peer-discussion on the application of the relaxation program.
  - b. *READY for MS facilitator meetings.*

### 6.2 Study participants and recruitment

#### 6.2.1 Participant eligibility

##### Inclusion criteria

- Diagnosis of MS [48]
- Age  $\geq 18$  years
- Written informed consent
- Resilience score  $< 83$
- Able to attend group sessions, and fluent Italian speaker

##### Exclusion criteria

- Severe cognitive compromise (Mini Mental State Examination  $< 19$ )
- Psychosis or other serious psychiatric conditions
- Psychotherapy in the preceding six months
- Prior formal training in mindfulness methods or current meditation practice
- Severe suicidality, including ideation, plan and intent
- One or more relapses in the previous month
- Corticosteroid treatment during the previous month
- Other serious medical disorders in addition to MS
- Current pregnancy
- MS diagnosis for less than three months

### 6.2.2 Recruitment and trial procedures

A flyer, which includes a general overview of the study and contact details, will be sent via e-mail to the patients of the participating MS Centres by the MS Centre team. People who show interest in participating in the study will be contacted by the study coordinator or centre Principal Investigator (PI). Subsequently, one trained clinical psychologist (Italian READY for MS facilitator) makes an appointment with those patients who met the inclusion criteria and agreed to participate in the study, and checks all eligibility criteria. She/he sends an e-mail to the participant with the link to the website containing the set of questionnaires. The total assessment will last about 55 minutes in each time-points (additional 20 minutes at T1 and T2 for filling in the satisfaction questionnaire). Each centre will collect information on the number of people approached, screened, and eligible prior to random assignment, with reasons for non-enrolment. Participants will be then assigned to the Italian READY for MS or control condition. Randomization will be provided by an independent randomization unit, using computer-based cluster randomization with minimization [49] (2 factors: Centre and CDRISC score  $< 50$  and  $\geq 50$ ). Groups will be allocated to Italian READY for MS or control intervention in a 1:1 ratio. Confirmation e-mails will be sent to the study coordinator and centre PI. The interventions will start within two weeks of the baseline assessment.

### 6.2.3 Withdraw

Participants will be free to withdraw from the study at any time, without giving reasons and with no risk of prejudicing future care. Study personnel will make every effort to obtain, and record, information about the drop out reasons.

### 6.2.4 Pre-study interview and informed consent (visit 0)

During the pre-study evaluation each potential participant receives full and adequate verbal and written information about the nature and purpose of the study. A written, signed informed consent is obtained, according to the Declaration of Helsinki and to the GCP Guidelines of the EU. The informed consent form will be kept on file by the study personnel and will be available for inspection by regulatory authorities or authorized persons.

### 6.2.5 Assessments

PROMs will be assessed immediately before (baseline visit, T0), after the booster session (T1, 12 weeks after baseline visit), at three (T2, 24 weeks after baseline visit), and six month follow-up (T2, 36 weeks after baseline visit) via web survey. The satisfaction questionnaire will be administered at T1 and T2. Participants will receive an e-mail with the link to the website containing the set of questionnaires.

## **6.3 Interventions**

Each group will be composed of 8-10 participants, a total of 8 groups will be performed (four Italian READY for MS and four relaxation); within each arm, the groups will be homogeneous assembled so that PwMS will be as much homogeneous as possible in terms of CD-RISC 25 scores. The Italian READY for MS groups will be run by a psychologist of the “Rete Psicologi AISM” who participated and successfully completed “The ACT and be READY for MS training program”. To

limit possible involuntary contaminations, the control group will be run by a psychologist not involved in “The ACT and be READY for MS training program” and with no expertise in ACT or mindfulness interventions. Each group will be run in a dedicated room of the Hospital/Institute of each participating MS Centre. Participants will be asked not to disseminate information or materials of the program in which they are allocated. In addition, READY for MS and relaxation groups will be scheduled in order to prevent contact between participants of the two groups. Facilitators will be asked not to disseminate information or materials with the colleagues who are running the other intervention.

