## 6.5 Data analysis

### 6.5.1 Sample size calculation

The sample size calculation was based on the results from the pilot study [paper under review], where we found a mean change in the CD-RISC 25 at 3-month follow-up in the READY for MS arm equal to 15.61 (standard deviation, SD: 13.63, n=18) vs. a mean change in the relaxation arm equal to 5.95 (SD: 14.11, n=19). Moreover, we estimated an intra-cluster correlation coefficient (ICC) equal to 0.08.

A sample size of 12 clusters per treatment arm (total number of clusters=24) with 10 individuals per cluster (total sample size 240) achieves 94.6% power to detect a mean difference of 9.66 between the two arms in terms of change in CD-RISC 25 at 3-month follow-up [59]. The SD of change in the CD-RISC 25 at 3-month is assumed equal to 14.53. The ICC is assumed, conservatively, equal to 0.10. The type I error (alpha) is assumed to 0.05.

Starting from the previous scenario (i.e. total sample size 240, 24 clusters, 10 subjects per cluster), we computed the study power assuming three scenarios of drop-out.

#### Scenario 1

Assuming a drop-out of 20% uniformly distributed among clusters (i.e. two individuals lost within each cluster): 12 clusters per treatment arm (total number of clusters=24) with eight individuals per cluster (total sample size 192) achieves 92.1% power to detect a mean difference of 9.66 between the two arms in terms of change in CD-RISC 25 at 3-month follow-up [59]. The SD of change in the CD-RISC 25 at 3-month is assumed equal to 14.53. The ICC is assumed, conservatively, equal to 0.10. The type I error ( $\alpha$ ) is assumed to 0.05.

#### Scenario 2

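### Section 6.3 plans 8 groups (64–80 people), but the sample size rests on 24 groups (240 people); with 8 groups, power would be about 40–44%, not 94.6%

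*Protocol*

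**What the plan says.** Protocol section 6.3 (Interventions) sets the size of a group, "Each group will be composed of 8-10 participants", and in the same sentence the number of groups: "a total of 8 groups will be performed (four Italian READY for MS and four relaxation"). Multiplied out, this is 8 × 8 = 64 to 8 × 10 = 80 participants, with four groups in each arm.

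Section 6.5.1 (Sample size calculation) describes a trial three times as large: "A sample size of 12 clusters per treatment arm (total number of clusters=24) with 10 individuals per cluster (total sample size 240"). It says that this design "achieves 94.6% power to detect a mean difference of 9.66 between the two arms". The three drop-out scenarios that follow (92.1%, 92.0% and 91.8% power) all keep 24 groups and only reduce the number of people within them.

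Section 1 (Summary) describes a test of "superiority of Italian READY for MS over relaxation in a sample of 240 people with MS". Section 2.1 refers to power above .91 with 25% drop-out, which is the 24-group calculation again.

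**The concern.** One document specifies two trials that differ threefold in size. Nothing in section 6.3 presents the 8 groups as a number per centre or per wave; it calls them a total.

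In a group-randomised trial the number of groups matters more than the number of people. It sets the standard error through the design effect, and it also sets the degrees of freedom of the test: 22 with 24 groups, 6 with 8 groups. Section 6.5.2 recognises the small-cluster problem by adopting the Kenward-Roger correction. A trial delivered as section 6.3 reads would more likely than not miss the effect it is designed to find, while still citing power above 90%.

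**Working it through.** **Inputs.** All come from section 6.5.1 unless noted.
- Difference in CD-RISC 25 change at 3-month follow-up: 9.66 (pilot 15.61 − 5.95).
- SD of change: 14.53.
- ICC: 0.10.
- Alpha: 0.05. Section 6.5.1 does not state sidedness. Two-sided is assumed here; section 6.5.2 uses two-sided tests, and two-sided reproduces the stated power.
- Allocation of groups: 1:1 (section 6.2.2).

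**Formulas**, with *k* groups per arm and *m* people per group:
- Design effect DE = 1 + (m − 1) × ICC
- SE = SD × √(2 × DE / (k × m))
- Noncentrality = 9.66 / SE
- Power from the noncentral *t* distribution with 2(k − 1) degrees of freedom

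**Step 1: reproduce the protocol's figures.**
- k = 12, m = 10: DE = 1 + 9 × 0.10 = 1.9; SE = 14.53 × √(3.8/120) = 2.586; noncentrality = 3.736; 22 df; power 94.6%. The protocol says 94.6%.
- k = 12, m = 8 (Scenario 1): DE = 1.7; SE = 2.734; noncentrality = 3.533; power 92.1%. The protocol says 92.1%.

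Other methods do not match. For 24 groups of 10, a normal approximation gives 96.2%, a *t* test with individual-level degrees of freedom 96.1%, and a one-sided test 97.6%. The two-sided test with cluster-level degrees of freedom is therefore taken as the protocol's method.

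**Step 2: the same method with the groups of section 6.3** (k = 4, 6 df).

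| People per group | Total | DE | SE | Noncentrality | Power |
|---|---|---|---|---|---|
| 10 | 80 | 1.90 | 4.478 | 2.157 | 44.2% |
| 9 | 72 | 1.80 | 4.595 | 2.102 | 42.4% |
| 8 | 64 | 1.70 | 4.736 | 2.040 | 40.4% |
| 7.5 (10 less 25%) | 60 | 1.65 | 4.819 | 2.005 | 39.3% |
| 6.4 (8 less 20%) | 51.2 | 1.54 | 5.040 | 1.917 | 36.5% |

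A simulation of group means (40,000 runs) agrees: 94.6% for 24 groups of 10, 44.5% for 8 groups of 10, and 40.5% for 8 groups of 8.

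**Step 3: sensitivity to the ICC.** Section 6.5.1 gives a pilot estimate of 0.08 and section 2.1 mentions .07. Power with 8 groups of 8 to 10 is:
- ICC 0.08: 43.3% to 47.8%
- ICC 0.07: 44.9% to 49.8%

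The normal approximation at ICC 0.10, which overstates the protocol's own figure, gives 53.2% to 57.8%.

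**Step 4: can the two counts be reconciled?**
- *Larger groups:* 240 / 8 = 30 per group, which section 6.3 excludes.
- *Eight per wave:* the monitoring schedule in section 8.2 suggests two enrolment waves. That gives 16 groups and 128–160 people, still short of 24 and 240. Power would be 76.5% (8 per group) to 81.0% (10 per group).
- *Eight per centre:* section 6.1 lists eight centres, giving 64 groups.
- *Carried over from the pilot:* section 2 reports four groups in the pilot.

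None of these readings works.

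**The case against.** The strongest reply is that the intended design is plain. The summary, the base case and all three drop-out scenarios agree on 240 people or 24 groups, and a single clause differs. Eight groups also sit badly with the rest of the protocol: spread over eight centres they average one per centre, although section 6.2.2 minimises on centre. The total appears to be managed centrally, because an independent unit randomises the groups and section 7 lets the steering committee offer outstanding groups to active centres. On this view the low power is hypothetical and the stated power is correct.

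Much of this stands. The power calculation is right, section 6.3 is the outlier, and 40–44% applies only if 8 groups are actually run. It is also true that 24 groups are what the stated 94.6% requires, not a minimum for any acceptable power: 16 groups of 10 would give about 81%. The range of 8–10 people per group is not a separate fault, since section 6.5.1 already gives 92.1% at eight per group and models under-filled groups.

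None of it removes the contradiction. That a reader can guess which number was meant does not make the protocol consistent, and the wrong number stands in the section on delivery of the groups.

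**Conclusion.** The protocol contradicts itself on the number of groups: 8 in section 6.3 against 24 in section 6.5.1, or 64–80 people against 240. Every power figure in the protocol depends on 24 groups. If the trial were run with the 8 groups of section 6.3, power for the planned difference would be 40–44% at the protocol's ICC of 0.10, and no more than about 50% at the lower ICCs it mentions, before drop-out. These figures assume a two-sided 5% test with cluster-level degrees of freedom, the method that reproduces the stated 94.6% and 92.1%. This must be corrected, because the trial's size and its ability to answer its question depend on it.

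**What to change.** Change section 6.3 to 24 groups, 12 Italian READY for MS and 12 relaxation, so that it agrees with sections 1 and 6.5.1. This is a one-line correction and adds no participants to the 240 already planned.

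The sponsor should confirm the intended count first, since the document does not show how many groups are resourced. If only 8 will be run, the change is a redesign: restate the sample size as 64–80 in sections 1 and 6.5.1, replace the power figures in sections 2.1 and 6.5.1 (about 40–44% before drop-out), and recompute the drop-out scenarios for 8 groups. The summary gives the sample size but no power, so only its sample size would change.
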